### Participant timeline {13}

The overall participant timeline is illustrated in Fig. 1.

**Fig. 1 Fig1:**
[figure not shown]
SPIRIT schedule of enrolment, intervention, and assessments

Week 1 (T1): Eligible participants will meet with a member of the research team at the laboratory or via an online assessment hosted using the Jane App, who will explain the study protocols and obtain consent (either written or via Qualtrics). Participants will be asked to complete the series of structured clinical interviews, self-report questionnaires via Qualtrics, and then are provided with an actigraphy device and a link to an online daily sleep diary to complete for a period of 7 consecutive days.

Week 2: Participants will be randomly allocated to CBT-I or TAU.

Weeks 2 to 6: If randomized to the treatment group, participants will be invited to attend 5 sessions of CBT-I in person or via telehealth. Participants in the TAU group will receive regular obstetric care provided according to the needs and current regime of the patient.

Week 7 (T2): After 7 weeks, all the participants will be invited to complete the same set of questionnaires from the baseline assessment. Additionally, participants will be sent an Actiwatch and a link to an online daily sleep diary to complete for a period of 7 days.

Six months postpartum (T3): At 6 months postpartum, all participants will be invited to a web-link with the same set of questionnaires from the previous points of assessment, as well as one additional questionnaire assessing infant sleep quality. Participants will also be sent an actiwatch and a link to an online daily sleep diary to complete for a period of 7 days.

### Sample size {14}

We used pre-post data available from our Phase IIb pilot trial, comparing in-person CBT-I to waitlist control (*η*^2^ = .41, *f* = 0.84), to conduct a power analysis. The effect size was large, and the power analysis indicated that we would need 18 participants to provide power over 90% to detect a clinically significant change of 8 points on the ISI [83]. Although longitudinal analyses of CBT-I show that gains are maintained up to two years posttreatment, we wanted to account for the possibility that the effects of treatment may decrease by 6 months postpartum. We therefore powered the RCT to detect a medium effect size (*﻿f* = 0.25), resulting in a total sample size of 44 participants (22 per group) over three assessment time points. Although retention in our studies has been excellent, we accounted for a potential attrition rate of 20% based on previous research in this area with longer follow-up periods [89], resulting in an initial total of 54 participants. When the protocol was amended due to the COVID-19 pandemic, 2 participants had to drop out of the intervention due to pandemic related schedule adjustments and we were unable to send actiwatches to 3 participants due to the temporary university closure. Therefore, the recruitment of 5 additional participants was needed to make up for the incomplete data and/or participation. To ensure there was a 1:1 ratio of participants per group, a final total of 62 participants will be recruited.

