There have been four studies to date [70–73] examining the effectiveness of in-person or digital CBT-I specifically in pregnancy, all showing positive results in favour of active intervention. Following the ORBIT model [74, 75], our research team conducted a Phase II open pilot trial of CBT-I for pregnant women with insomnia, demonstrating that it was effective in reducing both subjective symptoms of insomnia and improving objective indices of sleep quality [70]. Another research group conducted a multi-site randomized controlled trial (RCT) of CBT-I with an ethnically diverse sample of treatment naive women [71]. Results indicated reductions in insomnia severity, self-reported total wake time, and symptoms of depression. Two RCTs have examined the efficacy of digital CBT-I in pregnancy delivered online, with results indicating that a digital CBT-I program Sleepio (Big Health Inc.) was associated with reductions in insomnia severity and improvements in sleep duration and quality [72, 73].

With limited access to in-person services and increased fear of threat to the health of their baby during the COVID-19 pandemic [6], there is an unprecedented need for telehealth delivery of programs for pregnant women. Telehealth refers to the provision of health care services using technological modalities instead of, or in addition to, in-person methods, and include behavioural and/or mental health care (e.g., therapy using the phone, diagnostic interviews via videoconferencing, apps to track mood states, and email consultations) [76]. Telehealth adaptations of CBT-I also address barriers to accessing treatment reported by pregnant women, such as transportation, childcare and/or work hours [77–80]. The COVID-19 pandemic has served as a catalyst for the implementation of telehealth mental health care services [81]. Indeed, our team launched a Phase III randomized controlled trial of CBT-I for pregnant women comprising five individual in-person therapy sessions, however, when COVID-19 was declared a pandemic and physical distancing measures were enacted, we amended the protocol to deliver the intervention by telehealth (i.e., videoconferencing). This presents the unique opportunity to be the first study to investigate the efficacy of CBT-I delivered via telehealth during pregnancy.

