## Trial design {8}

A two-arm, single-blinded, parallel group randomized controlled trial (RCT) design with repeated measures will be used to evaluate the impact of CBT-I delivered in person or via telehealth for treatment of insomnia experienced in pregnancy compared to the TAU control group. Assessments will occur at baseline, between 12 and 28 weeks of pregnancy (T1), 1 week post-treatment (T2), and 6 months postpartum (T3).

This trial adheres to the Standard Protocol Items: Recommendations for Intervention Trials (SPIRIT) guidelines [82] and was registered with ClinicalTrials.gov (NCT03918057). All procedures were performed in accordance with the University of Calgary Conjoint Health Research Ethics Board (REB19-0465) and the 1964 Helsinki declaration and its later amendments. All participants provided informed consent prior to enrollment in the study.

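### The sample size section moves between two scales for f without saying so, so 44 women do not give usual power for a medium between-arm difference at 6 months postpartum

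*Protocol article*

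**What the plan says.** Everything is in the protocol article, Sample size {14}. The pilot effect is given as η² = .41, f = 0.84, and from it the section concludes that "we would need 18 participants to provide power over 90% to detect a clinically significant change of 8 points on the ISI". It then explains why it did not stop there: "we wanted to account for the possibility that the effects of treatment may decrease by 6 months postpartum". The next sentence lowers the target: "We therefore powered the RCT to detect a medium effect size", with f = 0.25, "resulting in a total sample size of 44 participants (22 per group) over three assessment time points". The 44 is raised to 54 for 20% attrition and to 62 after the pandemic changes.

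The section does not say which effect f = 0.25 measures. The schedule is in Trial design {8}: baseline (T1), one week after treatment (T2) and 6 months postpartum (T3). Objectives {7} expects an advantage for CBT-I at T2 that is maintained at T3.

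**The concern.** The section reads as one line of reasoning on one scale: a large effect of 0.84 needs 18 women, a cautious medium effect of 0.25 needs 44. A reader would conclude that the target was cut to less than a third, and that the trial has good power for a medium difference between arms at T3, where fading is feared.

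On the two-group scale a medium effect needs far more than 44 women, so the two steps cannot share a definition of f. If they do not, the safety margin described for T3 is much smaller than it looks, and the section credits the design with a sensitivity it lacks. An inconclusive T3 result could then be taken as evidence against a medium effect.

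**Working it through.** **Inputs from the document.** f = 0.84 with N = 18 and power over 90%; f = 0.25 with N = 44; three visits; two equal arms; 20% attrition; 62 randomized.

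**Assumptions.** Two-sided α = 0.05, equal SD at each visit, and a common within-woman correlation ρ (0.5 unless stated).

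**Step 1: reproduce the 18.** For a two-group F test, λ = f²N with 1 and N − 2 df. λ = 0.84² × 18 = 12.70 gives power 91.7%. N = 16 gives 87.7%, so 18 is the smallest balanced total for 90%. As an interaction f over two visits at ρ = 0.5, 8 women would do. The 18 is therefore a two-group figure, where d = 2f = 1.68 SD.

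**Step 2: reproduce the 44 at f = 0.25.**

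| Test | λ | Power at N = 44 |
|---|---|---|
| Two-group, one visit | f²N = 2.75 | 36.7% |
| Arm main effect over 3 visits, ρ = 0.5 | 3f²N / (1 + 2ρ) = 4.125 | 51.0% |
| Arm main effect over 3 visits, ρ = 0 | 3f²N = 8.25 | 80.1% |
| Arm-by-time interaction, ρ = 0.5 | 3f²N / (1 − ρ) = 16.5 | 95.6% |

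The interaction test has 2 and 2(N − 2) = 84 df. N = 42 gives 94.6%, so 44 is the smallest even N for 95% power. It is also the smallest for 90% at ρ = 0.4 and for 80% at ρ = 0.2. The ρ = 0 main effect also yields 44, but three uncorrelated visits from the same woman are not credible. On the two-group scale of Step 1, 80% power at f = 0.25 takes 128 women.

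**Step 3: what an interaction f of 0.25 means.** Let the between-arm differences at T1, T2, T3 be δ₁, δ₂, δ₃ in SD units. The interaction f is the root mean square of (δⱼ − mean δ)/2.
- Pattern 0, d, d: the deviations are −d/3, d/6, d/6, so f = d√(1/18) = 0.2357d. Then d = 0.25/0.2357 = 1.06 SD.
- Pattern 0, d, d/2 (effect halves by T3): f = 0.2041d, so d = 1.22 SD at T2.

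On one scale, the target therefore fell from 1.68 SD to about 1.06 SD, not from 0.84 to 0.25.

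**Step 4: power for a medium difference, d = 0.5, at one visit.** Two-sample t test; baseline adjustment at ρ = 0.5 divides the SD by 1/√0.75, that is, multiplies it by √0.75 = 0.866.

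| Per arm | Unadjusted | Baseline-adjusted |
|---|---|---|
| 22 (the planned 44) | 37% | 46% |
| 25 (62 × 0.8 = 49.6) | 41% | 52% |
| 31 (all 62 followed) | 49% | 61% |

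The interaction test that yields 44 gives 37% for d = 0.5 at both T2 and T3 (ρ = 0.5), and 29% if 0.5 SD at T2 halves by T3. At 22 per arm, varying ρ from 0.3 to 0.7 gives 28–55% for change scores and 40–62% for baseline-adjusted analysis.

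**Step 5: difference detectable at one visit with 80% power.**

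| Per arm | Unadjusted | Baseline-adjusted, ρ = 0.5 |
|---|---|---|
| 22 | 0.87 SD | 0.75 SD |
| 25 | 0.81 SD | 0.70 SD |

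The document gives no SD for the Insomnia Severity Index (ISI). If its 8 points correspond to 1.68 SD, the SD is 8/1.68 = 4.8 points, and 0.87 SD is about 4.1 points against 2.4 for 0.5 SD. For an assumed SD of 4 to 6, 0.87 SD is 3.5 to 5.2 points and 0.5 SD is 2 to 3.

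**The case against.** The best defence is that the 44 is right. It follows exactly from a standard 2 × 3 interaction calculation, and that reading suits the repeated-measures design, the outcome defined as change over all timepoints, and the GEE analysis. The section attaches the medium label to f, and never promises power for 0.5 SD at one visit. This stands to the extent that there is no arithmetic error. It does not rescue the label: one sentence earlier f is on the two-group scale, and the reason given for lowering it concerns the effect at T3.

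A second defence is that the design tolerates real fading. Half the pilot effect is 1.68/2 = 0.84 SD, for which a t test at T3 has 78% power with 22 per arm and 83% with 25 (88% and 92% baseline-adjusted, ρ = 0.5). This stands if the pilot f is a controlled, between-arm effect.

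A third is that the analysis may do better than a single-visit t test. Averaging T2 and T3 with baseline adjustment (ρ = 0.5) gives 63% for d = 0.5 with 22 per arm, 69% with 25 and 78% with 31. That also stands, but an average over both visits does not answer whether the effect persists at T3.

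Finally, a condensed article may leave the correlation and power to the full protocol. Agreed. The point here is what the article positively states, not what it omits.

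**Conclusion.** The point holds as one of labelling and stated sensitivity. The 18 and the 44 use different definitions of f, and the trial is not powered at the usual 80% for a medium between-arm difference (0.5 SD) at T3. Power there is 37% with 22 per arm, 41% with 25 (52% baseline-adjusted) and 49% (61%) with all 62. These figures assume two-sided α = 0.05 and, where adjusted, ρ = 0.5.

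Three stronger readings are not supported:
- *The 44 is miscalculated.* It reproduces exactly as an interaction figure.
- *The trial can detect nothing smaller than about 1 SD.* The 1.06 SD belongs to 95% power. At 80% the detectable difference is 0.83 SD by the interaction test (effect equal at T2 and T3, ρ = 0.5) and 0.87 SD by a single-visit t test.
- *The chance of seeing a medium effect is always below one half.* With baseline adjustment it is 52% at 25 per arm and 61% at 31.

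Nor does it follow that the trial is too small for its main purpose. Differences well above 0.5 SD, including half the pilot effect if that was controlled, remain within reach. The matter should be corrected, but it does not threaten the trial.

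**What to change.** Amend Sample size {14}; no further enrolment is asked for, and Trial status records that recruitment has finished.

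1. State that f = 0.25 is an arm-by-time interaction effect over three visits, if that is how the 44 was obtained, and that the f = 0.84 behind the 18 is a two-group effect.
2. Remove the description of 0.25 as a medium effect size.
3. Give the between-arm difference detectable at T2 or T3 with 80% power: about 0.87 SD with 22 per arm (0.75 SD baseline-adjusted, ρ = 0.5), or 0.81 SD (0.70 SD) with 25 per arm. Add the equivalent in ISI points under a stated SD.

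The change is to wording only. Its cost is that the stated sensitivity becomes less favourable than the section now implies.

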### Recruitment {15}

Participants will be recruited from Alberta, Canada, through ultrasound clinics and a low risk primary care maternity clinic, where they will be approached by a research assistant or can respond to the posted advertisements. Potential participants will also be able to self-refer through advertisements posted online (e.g., lab website and social media accounts including Facebook, Instagram, and Twitter). Those interested in participating will contact the investigators’ lab and receive additional information about the study protocols.

## Assignment of interventions: allocation

### Sequence generation {16a}

Participants will be randomly allocated in a 1:1 ratio to CBT-I or TAU. Randomization will be determined using an online research randomization tool (GraphPad Software), which is not predictable and eliminates potential experimenter bias [90]. Sixty-two participants will be enrolled in the RCT, with 31 randomized into each study group. 

### Concealment mechanism {16b}

Participant assignments will be placed into opaque envelopes that contain the results of the randomization.

### Implementation {16c}

A staff member who is not associated with the study will conduct the randomization and sequence generation. After the baseline assessment is completed, a research assistant will open the envelope and inform participants of their assignment.

## Assignment of interventions: blinding

### Who will be blinded {17a}

Participants and therapists will not be blinded to condition. The research assistants conducting the clinical interviews, administering psychological questionnaires, and coordinating completion of the actigraphy and daily diary assessments will be blinded to participants’ group assignment, as will be the psychologists supervising the follow-up diagnostic interviews.

### Procedure for unblinding if needed {17b}

Not applicable.

## Data collection and management

### Plans for assessment and collection of outcomes {18a}

#### Primary outcome

Self-reported measures of sleep are considered the gold standard for the primary outcome in clinical trials, as they are often more sensitive to treatment effects [91]. Insomnia symptoms will be assessed using the Insomnia Severity Index (ISI). The is a 7-item questionnaire designed to identify cases of insomnia and evaluate treatment outcomes [83]. The ISI assesses severity of sleep onset, sleep maintenance and early wakening problems, sleep dissatisfaction and perceived distress caused by sleep problems [92]. Higher scores on the ISI are indicative of more symptoms of insomnia [93]. The ISI has been reliably used to assess insomnia and response to CBT-I treatment during pregnancy [70, 71, 86].

#### Insomnia diagnosis

Insomnia diagnosis will be confirmed using the Structured Clinical Interview for DSM-5 Sleep Disorders (SCISD) [84], which produces reliable and valid insomnia diagnoses, and provides information about developmental course and impact [94].

#### Objective sleep measure

Objective sleep quantity and quality will be assessed using actigraphy (Actiwatch II, Phillips, USA). Actigraphy monitoring provides objective information on circadian rhythm amplitude, acrophase, and mesor as well as indices of sleep efficiency, sleep latency, total sleep time, and number and frequency of awakenings [95]. Actigraphy has been used in research involving pregnant women, mothers, and infants, and is considered a valid measure of sleep quality and quantity [96, 97] as it yields estimates that are highly correlated with polysomnography [98]. Consistent with actigraphy recommendations, participants will be asked to continuously wear the actigraph for seven days after each in-person assessment point [99, 100].

#### Patient-reported sleep measures

Daily sleep diary logs will be used to measure total sleep time, time in bed, sleep efficiency, sleep onset latency, and number of awakenings [101]. Sleep diaries will be used to verify actigraphy data, and changes will be made to sleep intervals only when a manual calculation error was observed, for example, if a rest interval was identified when a participant indicated that she had not been wearing the watch. The Pittsburgh Sleep Quality Index (PSQI) is a 19-item instrument assessing sleep quality during the previous month [2]. There are seven components of the PSQI and these are subjective sleep quality, sleep latency, sleep duration, habitual sleep efficiency, sleep disturbances, use of sleeping medications and daytime dysfunction. A score above 7 has been used in other studies during pregnancy to indicate poor subjective sleep quality [15]. The PSQI has been validated against polysomnography and used reliably among pregnant women [102–104].

#### Secondary outcomes

*Symptoms of depression* will be assessed with the Edinburgh Postpartum Depression Scale (EPDS) [105]. The EPDS consists of 10 items, and is a reliable and valid tool for identifying symptoms of depression in pregnancy and the postpartum [106]. We will also collect information about psychiatric diagnoses from the SCID-5 [107].

*Infant birth outcomes*, including information about preterm birth (e.g., gestational length), delivery type, and birth weight, will be gathered through linkage to participants’ heath records for the Alberta Perinatal Health Program.

#### Exploratory outcomes

##### Symptoms of anxiety

The Pregnancy Specific Anxiety (PSA) measure assesses the degree to which pregnant women have felt anxious, concerned, afraid, and panicky in the preceding week [108, 109]. The PSA is a reliable and valid indicator of anxiety about pregnancy-related issues, with strong face validity and predictive validity, and will be used to assess anxiety experienced during pregnancy [108, 109]. The Strait Trait Anxiety Inventory (STAI-6) will be used to measure both state anxiety (around a specific situation) and trait anxiety (as a personality trait), with acceptable reliability and validity [110].

##### Infant sleep

Subjective ratings of infant sleep will be obtained by maternal report using the Brief Infant Sleep Questionnaire (BISQ). The BISQ asks parents about their infant’s regular sleep patterns so an average sleep pattern for the infant can be determined [111]. This questionnaire has shown high test-retest correlations (*r *> .82) and been found to be highly correlated with measures such as sleep diaries and actigraphy [111].

#### Descriptive measures

Data will be collected regarding demographic and psychosocial variables known to impact sleep. Demographic information collected will include age, family socioeconomic status, and number of children at home. Health practices assessed include smoking, alcohol consumption, and level of habitual exercise. Assessment of previous mental health problems, sleep disorders, and psychotropic medication use will be assessed via interview.

### Plans to promote participant retention and complete follow-up {18b}

Research assistants will contact participants to book assessments. Scheduled study-related reminders for assessments and therapy sessions will be sent to participants through the Jane app service.

### Data management {19}

Data will be stored on a secure server in accordance with the University of Calgary’s Data Retention Policy. Only the primary investigator and study coordinators will be given access to the study folders where the database is saved.

### Confidentiality {27}

Patient confidentiality will be protected through all phases of assessment, treatment, and data analysis in accordance with University of Calgary ethics guidelines. All study personnel will sign a confidentiality/non-disclosure agreement form prior to their involvement in the study.

Participants will be forewarned that absolute confidentiality cannot be provided in a lab setting or online; others present may recognize the fact of their research participation, and information transmitted via the internet may not be completely secure. However, individual data provided by participants will be de-identified and anonymized to protect their privacy and confidentiality. Any documents with identifiable information (e.g., consent forms, case notes, contact information) will be password protected and/or stored in a locked, secure area at the University of Calgary separately from anonymized data. We have also implemented telehealth policies in accordance with the College of Alberta Psychologists Practice Guidelines governing the delivery of Telepsychology Services [112]. Participants will become familiar with the limits to confidentiality during the informed consent process before participating in this study.

For purposes of reliability and supervision, in-person therapy sessions may be audio and/or recorded, with participants’ permission. The contents of the taped sessions are confidential and they will be stored in a secure location and will not be used for any other purpose. The tapes will be erased after they have served their purpose. The recordings will be viewed only by the licensed clinical psychologist who will supervise the administration of the intervention and the team of graduate level practicum students who will deliver in-person therapy.

### Plans for collection, laboratory evaluation, and storage of biological specimens for genetic or molecular analysis in this trial/future use {33}

Not applicable.

## Statistical methods

### Statistical methods for primary and secondary outcomes {20a}

Categorical variables will be analyzed using chi-square tests. Ordinal variables will be analyzed using nonparametric tests in addition to using Student’s *t* tests. Independent-samples*t* test, *χ*^2^ test, and Fisher’s exact test will be used to compare the groups on demographic characteristics known to influence sleep, such as age, parity, body mass index, and socioeconomic status; covariates found to differ between groups will be controlled for in subsequent analyses. Primary analyses of insomnia severity will be conducted using generalized estimated equations (GEE) and an intent-to-treat (ITT) approach. Other sleep measures including insomnia diagnosis, self-reported sleep quality, and actigraphy parameters will also be assessed using GEE. Secondary response variables including diagnosis and symptoms of depression, as well as preterm birth, will be examined. Changes in binary outcomes will be tested using GEE with a binary outcome specified.

